# A multi-centre, double-blind, randomized, placebo-controlled trial to evaluate the effectiveness and safety of ramelteon for the prevention of postoperative delirium in elderly cancer patients: a study protocol for JORTC-PON2/J-SUPPORT2103/NCCH2103

**DOI:** 10.1093/jjco/hyad061

**Published:** 2023-06-20

**Keywords:** ramelteon, delirium, randomized controlled trial, cancer

## Abstract

Postoperative delirium is an important issue in cancer patients, affecting surgical outcomes and the quality of life. Ramelteon is a melatonin receptor agonist with high affinity for MT1 and MT2 receptors. Clinical trials and observational studies in Japan, including in surgical cancer patients, have shown efficacy of ramelteon in delirium prevention, with no serious safety concerns. However, clinical trials from the USA have reported conflicting results. A Japanese phase II study investigated the efficacy and safety of ramelteon for delirium prevention following gastrectomy in patients aged ≥75 years, with findings suggesting the feasibility of a phase III trial. The aim of this multi-centre, double-blind, randomized placebo-controlled phase III trial is to evaluate the effectiveness and safety of oral ramelteon for postoperative delirium prevention in cancer patients aged ≥65 years as advanced medical care. The trial protocol is described here.

## Introduction

Delirium is an acute disturbance of consciousness that occurs in response to surgical invasion in about half of all hospitalized older people (1). It causes cognitive dysfunction including impaired attention, hallucinations, delusions and other thought disturbances, as well as impaired communication, which can cause distress to the patient, their family and medical staff; even if resolved, it can result in reduced independence, increased mortality and cognitive decline (2). It is also associated with a substantial cost burden, with a recent systematic review reporting per-patient costs of delirium ranging between US$806 and US$24 509 (3). Delirium is an important issue in oncology and palliative medicine, reducing surgical outcomes and quality of life. According to previous research, delirium (54.7%) was cited more than pain (46.9%) as a symptom that palliative physicians struggled to manage during supportive and palliative care (4). The incidence of postoperative delirium is substantial. We previously reported that delirium occurred in 32% of patients after surgical resection of cancer (5). Furthermore, in line with the aging population, the number of cancer resections in older people is increasing, with older people being at a high risk of postoperative delirium. Nevertheless, despite its burden and impact, no drug to date has been shown to be both safe and effective in preventing delirium, and as a result, there is no established method for its prevention (6).

Previous studies have demonstrated that excessive inflammatory response and elevated dopamine levels in peripheral blood are involved in postoperative delirium (7). Melatonin has the effect of reducing the inflammatory response to invasion and suppressing dopamine release (8,9). As insomnia appears to be a modifiable risk factor for delirium, it is plausible that melatonin may prevent delirium by improving sleep (10). The development of novel melatonin-based prophylaxis against delirium has been proposed as a potential approach but has not yet been initiated in Japan or overseas (11). Additionally, the discontinuation of medications that might increase the risk of delirium is recommended as part of combined interventions (12). It has been suggested that ramelteon, a melatonin receptor agonist with high affinity for MT1 and MT2 receptors (13), may be effective in preventing delirium through allowing the discontinuation of benzodiazepines and non-benzodiazepines, which are risk factors for delirium (14).

Ramelteon was approved in Japan in 2010 for treating insomnia (15). Observational studies in Japan have reported the consistent efficacy and safety of ramelteon in preventing postoperative delirium (14,16–18). A phase II study demonstrated the efficacy and safety of ramelteon for the prevention of delirium after gastrectomy in gastric cancer patients aged ≥75 years (19). These findings suggest the feasibility of a phase III trial.

A recent network meta-analysis of pharmacological interventions for delirium reported ramelteon to be the most promising drug for the prevention of delirium (20). The dual orexin receptor antagonist suvorexant appears to have similar efficacy to ramelteon (20). However, it has a mild risk of dependence and is listed as a Schedule IV drug by the Food and Drug Administration (21), raising concerns about its use in prophylaxis. Ramelteon has been shown to be effective and safe for the treatment of delirium associated with acute illness in randomized controlled trials conducted in Japan (22,23). Two randomized controlled studies in the USA investigated the efficacy of ramelteon in preventing delirium in patients undergoing orthopaedic surgery (24) and pulmonary thromboendarterectomy (25). Both studies reported that the drug was not effective in preventing postoperative delirium, in contrast to Japanese studies suggesting efficacy (14,16–19).

In summary, the efficacy of the melatonin receptor agonist ramelteon for treating delirium has not yet been conclusively established. We hypothesize that ramelteon may offer an effective and safe new standard of care for the prevention of postoperative delirium after cancer resection, and we plan to conduct a phase III trial to resolve this off-label use under Japan’s Advanced Medical Care System.

## Protocol digest of JORTC-PON2/J-SUPPORT2103/NCCH2103

### Trial registration and institutional review board approval

The study protocol has received ethical approval from the Clinical Research Review Committee of the National Cancer Center Hospital (CRB3180008). The trial is registered in the jRCT clinical trials registry: jRCTs031210673. The physician approved as the researcher by the Clinical Research Review Committee of the National Cancer Center Hospital (CRB3180008) will obtain written consent from each study participant using an informed consent form.

### Advanced medical care system

In Japan, ramelteon has already received manufacturing and marketing approval under the Pharmaceutical Affairs Law for the treatment of difficulty falling asleep in insomnia but not for the prevention of delirium. To investigate off-label use under the National Health Insurance system, this clinical trial has been approved by the Ministry of Health, Labour and Welfare's ‘Advanced Medical Care System’ (26). If a certain level of results is achieved under the Advanced Medical Care System, it is then possible to expand insurance coverage to include off-label use of ramelteon for treating delirium as an unapproved drug subject to the Expedited Practical Application Scheme for Unapproved Drugs.

### Aims

This study aims to evaluate the effectiveness and safety of oral ramelteon for the prevention of postoperative delirium in elderly cancer patients in Japan.

### Study design

The study is a multi-centre, double-blind, placebo-controlled, randomized controlled trial. The flowchart of the study procedure is shown in Fig. 1.

**Figure 1 f1:**
[figure not shown]
Flowchart of the study procedure.

### Study setting and patients

Cancer patients aged ≥65 who are scheduled to undergo surgery under general anaesthesia and hospitalization for at least 5 days after surgery at the National Cancer Center Hospital (Tokyo), East Hospital (Chiba) or Kinki Central Respiratory Center (Osaka) will be included. The study will take place from April 2022 to March 2024, with a 12-week follow-up period.

### Eligibility criteria

Patients who meet all the following criteria are eligible:

Patients with pathologically confirmed malignancy and patients with a strong clinical suspicion of malignancy.Patients aged ≥65 years at the time of registration.Patients scheduled for surgery under general anaesthesia and hospitalization for at least 5 days postoperatively.Patients eligible for oral or nasogastric tube medication preoperatively and who are expected to resume oral or nasogastric tube medication within 2 days postoperatively.Patients whose written consent to participate in the study has been obtained from them. Patients who have given their verbal and written consent in the presence of a witness (other than those engaged in the clinical research) and signed by the witness.

### Exclusion criteria

Patients in whom any one of the following applies are excluded:

Patients with a Diagnostic and Statistical Manual of Mental Disorders-5 (DSM-5) (27) diagnosis of delirium at the time of enrolment.Patients with a history of allergy to ramelteon.Patients with severe hepatic dysfunction defined as aspartate transaminase >90 U/L, alanine transaminase (ALT) >126 U/L (men), ALT >69 U/L (women) and total bilirubin >2.25 mg/dl.Patients who were participating in a clinical trial or clinical study with a new drug within 4 weeks of enrolment, including the date of enrolment (patients who have completed protocol treatment and are in the observation period are excluded).Patients taking ramelteon within 2 weeks of registration, including the date of registration, and fluvoxamine, with which there is a known interaction (28).Patients who have taken an orexin receptor antagonist (suvorexant or lemborexant) within 2 weeks of enrolment, including the date of enrolment.Patients with a history of epilepsy, Parkinson’s disease or dementia with Lewy bodies.Patients with a history of lactose intolerance.Patients whose planned resection includes central nervous system and intracranial areas.Patients with drug or alcohol use disorders within 5 years of enrolment, including the date of enrolment; patients who consume an average of 60 g of alcohol daily (e.g. 3 g of sake, three medium bottles of beer and five glasses of wine) or more; and patients with alcohol-related diseases (e.g. alcoholic liver disease).Patients who have previously participated in this study.Patients with moderate or severe dementia (Mini-Mental State Examination Japanese Version score < 21) (29).Patients with severe visual, hearing or reading impairments.Patients deemed unsuitable by the principal investigator or sub-investigator.

### Endpoints

The primary efficacy endpoint is the proportion of patients aged ≥75 years with delirium in the first 5 days after surgery as diagnosed by a trained psycho-oncologist using the DSM-5 (27). The secondary efficacy endpoints are as follows:

Delirium in the first 5 days after surgery as diagnosed by a psycho-oncologist using the DSM-5. This will be verified only if a significant effect is found in the primary analysis population. If a significant effect is not found in the primary analysis population, this will be analysed as an exploratory endpoint only.The remaining secondary endpoints will be investigated in all age groups and using stratified analyses (stratified into patients aged ≥75 years).The proportion of delirium in the first 5 days after surgery as diagnosed by psycho-oncologists using the DSM-5 (excluding delirium within 2 hours after surgery).Proportion of delirium in the first 5 days after surgery as assessed by nurses using the Nursing Delirium Screening Scale (Nu-DESC) (30).Delirium severity at 5 days after surgery as assessed using the Japanese version of the Delirium Rating Scale (DRS)-R-98 (31,32) and Nu-DESC.The proportion of cases of severe delirium in the first 5 days after surgery diagnosed by DSM-5 and DRS-R-98.Days from diagnosis to resolution of delirium according to DSM-5.Direct medical costs from post-surgery to discharge.Postoperative hospital stay.The proportion of antipsychotic use in the first 5 days after surgery.The proportion of patients stopping or withdrawing from benzodiazepines and non-benzodiazepines on the day prior to surgery.The proportion of falls, self-removal of any tubes including drip infusions and self-extubation and physical restraint within 5 days of surgery.Serum C-reactive protein level on the morning of the first postoperative day.Percentage of postoperative complications [Clavien–Dindo (CD) category grade ≥ 2] in the first 5 days after surgery.The proportion of postoperative complications (CD grade ≥ 2) within 90 days of surgery.Survival within 30 days after surgery.Survival up to 90 days after surgery.Recurrence-free survival within 90 days after surgery.Patient satisfaction with study participation and subjective symptoms on postoperative day 5 (Edmonton Symptom Rating System, modified Japanese version) (33).Percentage of patients who cannot be discharged home.Proportion of delirium in the first 5 days after surgery diagnosed by a psycho-oncologist using the DSM-5, with a Pittsburgh Sleep Quality Index (PSQI) (34) of ≥6 and a PSQI of ≤5 at enrolment.

### Safety assessments

Safety assessments include adverse events and adverse reactions during the treatment period until postoperative day 5. Investigation items for safety assessment are somnolence, floating dizziness, malaise, headache, constipation, nausea and urticaria. Adverse events related to surgery will not be included in this study. The investigator or sub-investigator will consult with the surgeon at each site to determine whether an adverse event is surgery related. Common Terminology Criteria for Adverse Events v5.0 grade 2 or higher will be treated as an adverse event.

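### Adverse events judged surgery related are left out of the safety data, so a drug-caused event misjudged as surgical is lost from the placebo comparison

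*Protocol article*

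**What the plan says.** Safety shares the stated aim with effectiveness: the trial is to "evaluate the effectiveness and safety of oral ramelteon for the prevention of postoperative delirium" (Aims). The design is double-blind, randomised and placebo-controlled (Study design).

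The section Safety assessments sets these rules:

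- Window: "Safety assessments include adverse events and adverse reactions during the treatment period until postoperative day 5".
- Solicited symptoms: "Investigation items for safety assessment are somnolence, floating dizziness, malaise, headache, constipation, nausea and urticaria".
- Severity threshold: "Common Terminology Criteria for Adverse Events v5.0 grade 2 or higher will be treated as an adverse event".
- Exclusion: "Adverse events related to surgery will not be included in this study".
- Who decides: "The investigator or sub-investigator will consult with the surgeon at each site to determine whether an adverse event is surgery related".

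The section gives no criteria for the surgery-related judgement, no exemption for the seven symptoms, and no tabulation of the removed events by arm. Note 5 to Table 1 asks for the same symptoms to be investigated, but does not say that they escape the exclusion.

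**The concern.** Every patient has surgery under general anaesthesia. Apart from any preoperative dosing, the safety window is the first five postoperative days, when a surgical explanation is always at hand. Somnolence, dizziness, malaise, headache, constipation and nausea are common after anaesthesia and surgery. That is general clinical knowledge, not a statement in the article. Urticaria is the one listed item that is not a typical postoperative symptom.

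Randomisation spreads the surgical background evenly, so a by-arm count of all events already separates drug from surgery on average. The exclusion puts an individual causal opinion in front of that comparison, on top of the grade 2 threshold.

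At stake is how far a reassuring safety result can be trusted. Ramelteon is given here as prophylaxis, to patients who may never become delirious. The section on the Advanced Medical Care System says the results could support wider insurance coverage, and Statistical analysis would call the treatment useful on efficacy superiority. Events not included in the safety data may not be recoverable at analysis.

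**Working it through.** **1. The plan's own figures.** The article gives no adverse event rate, attribution fraction or safety power. The only computable design figures are the sample sizes, which serve to check the formula:

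n per arm = [1.960·√(2p̄(1−p̄)) + 1.282·√(p₁(1−p₁)+p₂(1−p₂))]² / (p₁−p₂)²

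- Age ≥75, 24% v 36%: (1.2702 + 0.8234)² / 0.0144 = 304.4, so 305 per arm and 610 in total, as stated.
- Age ≥65, 22% v 33%: (1.2377 + 0.8031)² / 0.0121 = 344.2, so 345 per arm and 690 in total, as stated.

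The 345 per arm is used below as the evaluable number after dropout.

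**2. What the filter does.** Let the true rates be p_C on placebo and p_C + Δ on ramelteon. Let a fraction b of background events and a fraction e of drug-caused excess events be judged surgical and removed. Then:

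- recorded placebo rate = p_C(1−b)
- recorded ramelteon rate = p_C(1−b) + Δ(1−e)
- recorded excess = Δ(1−e)

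So the recorded absolute excess falls whenever e > 0. If b = e (no discrimination), both rates shrink by the same factor and the risk ratio is unchanged. If b > e, the risk ratio rises.

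**3. Illustration.** Assumed, not from the article: p_C = 10%, Δ = 8 points, two-sided 5%, 345 per arm. Power = Φ[(d − 1.960·s₀)/s₁], where d is the recorded excess, s₀ the pooled and s₁ the unpooled standard error.

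Unfiltered: s₀ = √(2·0.14·0.86/345) = 0.02642 and s₁ = √((0.10·0.90 + 0.18·0.82)/345) = 0.02624. Then (0.08 − 0.05178)/0.02624 = 1.075, and power is 0.86.

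| Background removed (b) | Excess removed (e) | Recorded rates | Excess (points) | Risk ratio | Power |
|---|---|---|---|---|---|
| 0 | 0 | 10% v 18% | 8.0 | 1.80 | 0.86 |
| 25% | 25% | 7.5% v 13.5% | 6.0 | 1.80 | 0.73 |
| 50% | 50% | 5.0% v 9.0% | 4.0 | 1.80 | 0.54 |
| 75% | 75% | 2.5% v 4.5% | 2.0 | 1.80 | 0.30 |
| 90% | 90% | 1.0% v 1.8% | 0.8 | 1.80 | 0.14 |
| 50% | 40% | 5.0% v 9.8% | 4.8 | 1.96 | 0.67 |
| 50% | 20% | 5.0% v 11.4% | 6.4 | 2.28 | 0.87 |

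The last two rows let the judgement have some accuracy.

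**4. Other assumed rates, no discrimination, 50% removed.** At 20% v 28%, power goes from 0.69 to 0.37. At 5% v 10%, it goes from 0.70 to 0.41.

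**The case against.** **Attribution may carry information.** If clinicians remove background events more readily than drug-caused ones, the filter also removes noise. In the 50%/20% case power is about 0.87, no worse than unfiltered. This stands: the low power figures describe zero discrimination and are not a forecast. It does not rescue the rule, because the excess is still understated (6.4 points instead of 8), and keeping the events with a flag retains whatever the judgement is worth.

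**Blinding.** A reader might infer that the rule tilts the safety comparison in favour of ramelteon. The documents do not support that. The judgement is made in a double-blind trial, so no direction of bias between arms is shown. What remains is under-counting.

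**Other outcomes are not filtered.** A reader might also infer that these harms vanish from the trial. That goes too far. Under Endpoints, Clavien–Dindo grade 2 or higher complications, subjective symptoms on day 5, falls within 5 days and survival to 30 and 90 days carry no such exclusion. Dosing starts before surgery, and events before surgery cannot be surgery related. These recapture part of the harm, but on other scales or at one time point, and as secondary efficacy endpoints. None gives adverse event counts by arm for the seven symptoms.

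**No safety test is planned.** The article states no safety hypothesis or safety power, so power at 5% is only a yardstick. This is fair, but the understated absolute risks need no test to matter.

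**Condensed article.** The full protocol may say more on collection. But the exclusion is an explicit rule, not an omitted detail.

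**Conclusion.** The point holds as a defect in how safety is counted. The protocol excludes adverse events on a case-by-case causal judgement, with no exemption for solicited symptoms that overlap with ordinary postoperative ones, although the placebo arm already handles the surgical background. Any drug-caused event misjudged as surgical is lost, so recorded absolute risks and the absolute excess are understated.

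The size is unknown. Under the assumed 10% v 18% with 345 per arm, power ranges from about 0.87 (50% of background and 20% of excess removed), through 0.67 (50%/40%), to 0.54 and 0.14 (50% and 90% removed without discrimination), against 0.86 unfiltered. The rates and fractions are all assumptions.

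This should be fixed, but it does not threaten the trial's main result: the primary endpoint, sample size and efficacy conclusion are untouched.

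**What to change.** Replace the exclusion sentence with:

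> Adverse events of CTCAE grade 2 or higher from first dose to postoperative day 5, at minimum the seven listed items, are recorded and tabulated by arm regardless of judged cause. The surgery-related judgement is recorded as an attribute and used for a supportive table.

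The investigator already has to consider these events and consult the surgeon, so the change is to keep and flag them instead of leaving them out. The sample size does not change. The cost is more recorded events and higher crude rates in both arms. How much more is not known from the article, and recording every grade 2 or higher event in this population could bring in a good deal of surgical morbidity. If that load is a concern, limiting the rule to the seven listed items would still meet the point.

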### Treatment methods

A flowchart of the study procedure is shown in Fig. 1. The study schedule is shown in Table 1. The test drug comprises Swedish orange capsules filled with ramelteon 8 mg formulation and an identical control capsule containing a lactose tablet of the same specification (same size and weight but ramelteon-free). One capsule of the study drug (test or control) will be administered orally or via a nasogastric tube once daily before bedtime during the medication period (double-blind). As a co-intervention, a combined intervention for the prevention of delirium will be implemented in all patients, according to the National Institute for Health and Clinical Excellence Guideline ‘Delirium: prevention, diagnosis and management’, e.g. patients are provided clinically appropriate care if they have cognitive impairment, disorientation, dehydration, constipation, hypoxia, infection, immobility, pain, benzodiazepine and/or anti-benzodiazepine prescription, poor nutrition, sensory impairment and insomnia (12).

**Table 1 TB1:** Study schedule

[figure not shown]

Note 1: If the patient comes to the hospital after consent has been obtained and before preoperative admission, consent will not be obtained again.

Note 2: If the duration of administration can be secured, protocol treatment will start earlier during a period denoted by triangles.

Note 3: The Nursing Delirium Screening Scale will only be administered at the National Cancer Center Hospital.

Note 4: Details of the blood tests are as follows:

1. Total bilirubin, aspartate transaminase (AST) and alanine transaminase (ALT) at the date of registration are adopted from blood test results performed in clinical practice within 8 weeks retrospectively from the date of registration.

2. Adopt clinically performed blood test results for total bilirubin, AST, ALT and C-reactive protein on the first postoperative day.

Note 5: Adverse effects such as somnolence, floating dizziness, malaise, headache, constipation, nausea and urticaria should be investigated.

ALT, alanine transaminase; AST, aspartate transaminase; DRS, Delirium Rating Scale; DSM, Diagnostic and Statistical Manual of Mental Disorders; ESAS-r; Edmonton Symptom Assessment System Revised Japanese Version; Nu-DESC, Nursing Delirium Screening Scale

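### Grade 1 occurrences of the seven solicited symptoms are not counted as adverse events, so an excess of mild somnolence or dizziness on ramelteon could be missed

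*Protocol article*

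**What the plan says.** All references are to the protocol article.

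- **Aims.** Safety stands beside effectiveness: "This study aims to evaluate the effectiveness and safety of oral ramelteon for the prevention of postoperative delirium in elderly cancer patients in Japan".
- **Safety assessments, scope and window.** "Safety assessments include adverse events and adverse reactions during the treatment period until postoperative day 5".
- **Safety assessments, solicited items.** "Investigation items for safety assessment are somnolence, floating dizziness, malaise, headache, constipation, nausea and urticaria".
- **Safety assessments, first filter (cause).** "Adverse events related to surgery will not be included in this study".
- **Safety assessments, second filter (severity).** "Common Terminology Criteria for Adverse Events v5.0 grade 2 or higher will be treated as an adverse event".
- **Treatment methods, Table 1, Note 5.** The same seven symptoms appear again with no grade attached: "Adverse effects such as somnolence, floating dizziness, malaise, headache, constipation, nausea and urticaria should be investigated".
- **Endpoints.** One other patient-reported source is listed among the secondary efficacy endpoints: "Patient satisfaction with study participation and subjective symptoms on postoperative day 5", measured on the Edmonton scale.

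**The concern.** The protocol picks seven symptoms to ask about and then defines an adverse event so that the mildest grade of each does not qualify. The severity floor is separate from the surgery-relatedness filter. It acts on grade whatever the cause, and an event must pass both filters to be counted.

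The setting makes grade 1 worth seeing. A drug approved for difficulty falling asleep is given at bedtime to patients aged 65 or over who do not have delirium at enrolment. In prevention, even a mild excess of sleepiness or dizziness belongs in the balance of benefit and harm. If such an excess were confined to grade 1, the adverse-event table could show similar arms because of how events are counted, and a reader could take that as evidence of tolerability.

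**Working it through.** **1. Does any text exempt the seven items or provide for grade 1?**

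| Place | Covers the seven items? | Grade stated? | Comparison at grade 1? |
|---|---|---|---|
| Safety assessments | Yes, by name | Grade 2 or higher, no exception | No |
| Table 1, Note 5 | Yes, by name | None | None described |
| Endpoints, Edmonton scale | Patient-reported symptoms | Not CTCAE | One reading on day 5, listed under efficacy |

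Note 5 leaves open that grade 1 answers are collected, but it describes no analysis of them. The Edmonton scale is one reading and does not cover the treatment period. So the rule in Safety assessments governs the adverse-event comparison.

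**2. The plan's own figures.** The article gives no figure for the safety comparison. Its efficacy sample sizes reproduce with the usual two-proportion formula (pooled variance under the null, no continuity correction, two-sided 5%, power 90%):

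- Age 75 or over, 36% v 24%: 305 per arm, 610 in total; 610/0.9 = 677.8, so 678, as stated.
- Age 65 or over, 33% v 22%: 345 per arm, 690 in total; 690/0.9 = 766.7, against 766 stated, a rounding difference.

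These figures only supply the number per arm: 383 enrolled, about 345 after the 10% dropout allowance.

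**3. What the floor can do to the comparison.** Every symptom rate below is assumed, because the documents give none. Each patient is counted once, at worst grade. With *n* per arm, rates *p*₁ (ramelteon) and *p*₀ (placebo), and *p̄* their mean:

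- SE₀ = √(2·*p̄*(1−*p̄*)/*n*)
- SE₁ = √([*p*₁(1−*p*₁) + *p*₀(1−*p*₀)]/*n*)
- power = Φ((|*p*₁−*p*₀| − 1.96·SE₀)/SE₁)

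*Case A: the excess is spread in proportion across grades.* Any grade 15% v 10%, *n* = 383: SE₀ = √(2 × 0.125 × 0.875/383) = 0.0239, 0.05/0.0239 = 2.09, power about 55%. If one fifth of events are grade 2 or higher, the counted rates are 3% v 2%: SE₀ = 0.0113, 0.01/0.0113 = 0.89, power about 14%. With *n* = 345 the two powers are about 51% and 13%.

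The same pattern holds for other assumed rates with *n* = 383:

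| Any-grade rates | All grades | 50% are grade ≥2 | 30% | 20% | 10% |
|---|---|---|---|---|---|
| 18% v 10% | 89% | 58% | 38% | 27% | 15% |
| 10% v 5% | 75% | 45% | 29% | 21% | 12% |

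*Case B: the excess lies wholly at grade 1.* Grade 1 at 13% v 8%, grade 2 or higher at 2% v 2%. Any grade is again 15% v 10%, power about 55%. With the floor the true difference is 0, so the excess cannot be seen at any sample size. Grade 1 shown alone: SE₀ = √(2 × 0.105 × 0.895/383) = 0.0222, SE₁ = √((0.1131 + 0.0736)/383) = 0.0221, power = Φ((0.05 − 1.96 × 0.02215)/0.02208) = Φ(0.30), about 62%.

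*Case C: the excess lies wholly at grade 2 or higher.* Grade 1 at 8% v 8%, grade 2 or higher at 7% v 2%. Any grade is 15% v 10%, power about 55%. With the floor: SE₀ = √(2 × 0.045 × 0.955/383) = 0.0150, 0.05/0.0150 = 3.34, power about 92%. If grade 1 background is 40% in each arm, any grade becomes 47% v 42% and its power drops to about 28%, while the floor still gives 92%.

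In Case C grade 1 makes up 16 of the 25 percentage points of events (8 + 8 out of 15 + 10), yet the floor helps. What decides the effect is where the drug excess lies, not which grade is more common.

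**The case against.** The strongest case on the other side has four parts.

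**The text defines a term; it does not discard data.** A reader might infer that grade 1 symptoms are thrown away before the arms are compared. The article does not say that. It says what is treated as an adverse event, lists investigation items and adverse reactions besides, and in Note 5 asks for the seven symptoms with no grade limit. Grade 1 answers may be recorded, and the full protocol may tabulate them. This stands, so the point is limited to what is counted in the adverse-event comparison.

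**A floor can improve the comparison.** Malaise, nausea and constipation are plausible background after surgery under general anaesthesia. Randomisation keeps such background from causing bias but does not stop it from diluting a difference. This also stands. Case C shows that it is wrong to claim a loss of power whenever grade 1 predominates. It argues against replacing the grade 2 or higher summary with a pooled any-grade one, but not against showing the two side by side.

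**The figures are assumed and the remedy does not give an adequately powered test.** True: the rates and the grade split have no source in the article, and 15% v 10% at any grade reaches only about 51% to 55%. The calculations show direction under stated conditions and do not measure harm.

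**Nothing in the plan's decision turns on symptom rates.** A reader might also infer that the trial means to conclude there is no difference in somnolence or dizziness. The article states no safety test and no such conclusion. Its rule for judging ramelteon useful rests on superiority for delirium. The floor is prespecified, applies alike to both blinded arms and contradicts no other section. All of this is fair and keeps the point modest. Safety nevertheless remains a stated aim, and neither Note 5 nor the single Edmonton reading provides a grade 1 comparison.

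**Conclusion.** The concern holds in limited form. As written, grade 1 occurrences of the seven solicited symptoms do not count in the adverse-event comparison, and the article does not say whether they are recorded or shown elsewhere. This can hide an excess of mild somnolence or dizziness in a trial that sets out to assess safety.

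The size of the loss cannot be derived from the documents. On assumed rates of 15% v 10% at any grade with 383 per arm, it runs from complete (excess only at grade 1), through a fall from about 55% to about 14% power (excess proportional, one fifth of events at grade 2 or higher), to none, with a gain to about 92% (excess only at grade 2 or higher).

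This is a worthwhile, inexpensive improvement to safety reporting. It is not an error that touches the sample size, the primary efficacy analysis or the efficacy conclusion.

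**What to change.** In Safety assessments, add that the seven solicited symptoms are recorded at any CTCAE grade and tabulated by arm, with grade 1 and grade 2 or higher shown separately. Keep the grade 2 or higher summary, and keep the floor for unsolicited events. Align Note 5 to Table 1 by stating the same grade range. If the full protocol or case report form already does this, a sentence in the article saying so is enough.

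The cost is about one sentence of text and extra case report form entries for items already asked about. The downside is more background postoperative symptoms at grade 1. These can dilute a pooled any-grade comparison, which is why the grades must be shown apart and not only combined. No treatment, sample size or efficacy analysis changes.
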